## Abstract

**Background:**

Chlamydia is the most commonly diagnosed sexually transmitted infection (STI) in England and has serious public health consequences. Young people carry a disproportionate burden of infection. A number of social cognition models identify risk appraisal as a primary motivator of behaviour suggesting that changing risk appraisals for STIs may be an effective strategy in motivating protective behaviour. Meta-analytic evidence indicates that the relationship between risk appraisal and health behaviour is small, but studies examining this relationship have been criticised for their many conceptual and methodological weaknesses. The effect of risk appraisal on health behaviour may therefore be of larger size. The proposed study aims to examine the efficacy of an intervention to increase condom use intentions and behaviour amongst young people through changing chlamydia risk and coping appraisals. Coping appraisal is targeted to avoid the intervention being counterproductive amongst recipients who do not feel able to perform the behaviour required to reduce the threat. An experimental design with follow-up, a conditional measure of risk appraisal, and analysis which controls for past behaviour, enable the relationship between risk appraisal and protective behaviour to be accurately assessed.

**Methods/Design:**

The proposed study is a two-arm cluster randomised controlled trial using a waiting-list control design to test the efficacy of the intervention compared to a control group. Participants will be school pupils aged 13–16 years old recruited from approximately ten secondary schools. Schools will be randomised into each arm. Participants will receive their usual teaching on STIs but those in the intervention condition will additionally receive a single-session sex education lesson on chlamydia. Measures will be taken at baseline, post-intervention and at follow-up three months later. The primary outcome measure is intention to use condoms with casual sexual partners.

**Discussion:**

As far as the authors are aware, this is the first controlled trial testing the efficacy of an intervention to increase condom use intentions and behaviour through changing chlamydia risk appraisals. It is one of few experimental studies to accurately test the relationship between risk appraisal and precautionary sexual behaviour using a conditional measure of risk appraisal and controlling for past behaviour.

## Background

Chlamydia is the most commonly diagnosed sexually transmitted infection in England [1] and also across Europe [2]. It is frequently asymptomatic [3], and without treatment can lead to serious health consequences for women such as pelvic inflammatory disease, infertility and ectopic pregnancy. There is also growing evidence that it can cause infertility in men [4,5].

There is evidence that young people, who are disproportionately affected by chlamydia [6], may be underestimating the risk of infection. Studies have for example identified that important knowledge gaps exist [7-9] and that unhelpful beliefs may be influencing chlamydia risk appraisals in ways that reduce motivation to adopt protective behaviour [8].

A number of social cognition models include risk appraisal as a primary motivator of behaviour. These include the health belief model [10], the precaution adoption process [11] and protection motivation theory [12]. These models suggest that changing risk appraisals could be an effective strategy in motivating protective behaviour such as condom use.

The motivational hypothesis [13] asserts that preventative behaviour is the result of the desire to reduce one’s risk. It makes logical sense that to be motivated to take precautionary behaviour one has to perceive the consequences of inaction as serious and likely to occur. Systematic reviews examining the predictive relationship between risk appraisal and health behaviour have however largely found this relationship to be small [14,15], or absent in the case of sexual behaviour specifically [13]. This suggests that an intervention aiming to increase chlamydia risk appraisals will have either no effect or a weak effect on condom use intentions and behaviour.

The existing body of evidence however suffers serious problems which may have served to underestimate the relationship between risk appraisal and future behaviour. Following a review of nearly 60 studies examining this relationship, Weinstein and colleagues [16] concluded that a high proportion had serious conceptual and methodological flaws. These included the failure to control for past behaviour and the use of correlational data to examine the relationship between risk appraisal and behaviour. The use of correlational data to examine the relationship appears to be particularly common in studies of sexual behaviour [13]. Although cross-sectional designs always limit conclusions that can be drawn regarding cause-effect relationships, they are especially problematic when examining the motivational hypothesis. This is because risk appraisals are both a determinant and a product of risk behaviour. According to the motivational hypothesis, it is the belief that taking precautionary behaviour will be effective in reducing feelings of risk that motivates an individual to act. It follows that once preventative action is taken, feelings of risk are reduced. This means that when taking concurrent measures of risk appraisal and behaviour, a negative relationship should be expected. For this reason, Weinstein and colleagues [16] advise using longitudinal data, where risk appraisal is measured at time one, behaviour is measured at time two, and analysis controls for behaviour at time one.

A further methodological problem is that studies examining the motivational hypothesis have largely used ‘unconditional’ measures of risk. Unconditional measures are those which ask individuals to rate the probability of an adverse event occurring without indicating, for example, whether this is if they do or do not use a condom, whether this is with a long-term partner or a casual sexual partner. Using conditional measures of risk is preferable, as these questions elicit risk appraisals based on such moderating factors. Conditional measures of risk are not only more conceptually accurate but enable the relationship between risk and behaviour to be examined in a consistent and interpretable manner [17]. Weinstein and colleagues [16] advise that when testing the motivational hypothesis, that conditional measures of risk are taken in which individuals are asked to either rate their perceived vulnerability to the health threat if they continue with their existing levels of behaviour or if they take no precautionary action.

The present study will assess the efficacy of an intervention to change risk appraisals which overcomes the problems of much previous work in this area. The intervention is a single Sex and Relationships (SRE) lesson produced for the Health Protection Agency (HPA) and made available to teachers across ten European Union countries on their e-Bug website. The lesson was developed using Intervention Mapping [18,19] which provides a framework for developing theory- and evidence-based interventions. A detailed report on the development and content of the intervention can be accessed using this link (http://www.healthinterventions.co.uk/projects.aspx?section=10&item=78).

In addition to strategies to increase chlamydia risk appraisals, the chlamydia lesson incorporates strategies to raise condom use response efficacy (the perceived effectiveness of condoms in reducing the threat of chlamydia) and self-efficacy (beliefs about one’s own ability to use condoms). Protection Motivation Theory (PMT) [12] was developed based on the observation that increasing risk appraisals amongst individuals who do not believe that they are able to perform behaviour can be ineffective. PMT predicts that as individuals’ feelings of threat increase, that protective behaviour will also increase if they feel able to cope with that threat. If on the other hand they feel they can do nothing or little to change their behaviour, then increased perceptions of risk can be counter-productive leading to avoidance (e.g. avoid thinking about STIs), information derogation (e.g. ‘health related messages are over-hyped’), or threat minimisation (e.g. denying you’re at risk of STIs). Evidence concerning whether threat appraisal and coping appraisal (the combined effect of response and self-efficacy) interact or operate in parallel is inconclusive [15]. Until the nature of this relationship has been substantiated, interventions should seek to raise both threat and coping appraisals.

The proposed study uses a two-arm cluster randomised controlled trial (RCT) with a waiting-list control to test the efficacy of an intervention in increasing young adults’ condom use intention and behaviour through changing their chlamydia risk and coping appraisals. This will provide useful information about the ability of persuasive communication to bring about the desired programme effects. The waiting list control design has been chosen to allow all participants to benefit from the lesson. Cluster randomisation has been chosen to prevent within-school contamination.

The proposed study will use a conditional measure of risk. Given that a large proportion of the sample are not likely to be sexually experienced, participants appraisals of the risk of getting chlamydia if condoms aren’t used will be measured, rather than choosing the alternative ‘if continue with current behaviour’ option. In addition, this will be framed within the context of casual sexual partners for whom STI status is unknown given that this presents the most risky scenario. A further conditional stipulation will be vaginal sex, rather than oral or anal sex. The proposed study will also use an experimental design with follow-up for two months. Examining the motivational hypothesis in the context of an experimental study is ideal since delivery of the intervention should act to ‘destabilise’ existing chlamydia risk appraisals and reduce the predictive relationship between past and future behaviour for those who are already sexually experienced [16].

Whilst an experimental design affords the best circumstances for observing the motivational hypothesis, increasing chlamydia risk appraisals may not be sufficient to motivate condom use. Chlamydia is a single consequence of unprotected sex and evidence suggests that other outcomes of unprotected sex, such as the risk of pregnancy or making sexual experiences more enjoyable, may exert a more powerful effect on condom use intentions [20]. Other authors [13] have also drawn attention to the dyadic context of condom use decision making and the possibility that risk appraisals are not powerful enough to overcome other determinants of behaviour such as embarrassment discussing condom use or uncooperative partners. The proposed study will include a measure of condom use intention as well as behaviour. This is necessary because it is anticipated that a large proportion of the sample will be sexually inexperienced requiring the use of intention as the outcome measure in examining the motivational hypothesis. In addition, it will also enable examination of whether an increase in chlamydia risk appraisals is sufficient to increase condom use intentions and/or behaviour. This will enable conclusions to be drawn about whether a failure to change behaviour is the result of a failure to increase condom use intentions or to overcome the effect of stronger factors operating when intention is translated into behaviour.

### Research questions

#### Primary research question

•Is the lesson effective in increasing young people’s *intentions to use* condoms during vaginal sex with casual sexual partners?

#### Secondary research questions

•Is the lesson effective in increasing young people’s *condom use* during vaginal sex with casual sexual partners?

•If the lesson is effective, are changes in young people’s condom use intentions or behaviour due to changes in their chlamydia risk appraisals (perceived likelihood and severity) and/or coping appraisals (condom use response efficacy and self-efficacy)?

### Ethical review

This study has received ethical approval from Coventry University Ethics Committee.

## Methods/design

A two-arm cluster randomised controlled trial (RCT) using a waiting-list control will be used to test the efficacy of an intervention to increase young adults’ intentions to use condoms and actual use of condoms with casual sexual partners compared to a control group (see Figure 1). Secondary school pupils will be invited to participate. The intervention is a single lesson on chlamydia which aims to increase young adults’ chlamydia risk and coping appraisals. We hypothesise that there will be an increase in condom use intentions following delivery of the chlamydia lesson. At the two month follow-up, we hypothesise that there will be a higher rate of condom use during vaginal sex with casual sexual partners amongst sexually experienced participants in the intervention group compared with the control group. At two months, we will also measure condom use intentions to see whether any increases have been maintained over time. We hypothesise any effects of the intervention on condom use intentions or behaviour will be mediated by risk appraisals and/or coping appraisals.

**Figure 1 F1:**
[figure not shown]
Study design.

### Participant recruitment and baseline assessment

The study will take place in approximately ten schools across England. All schools will be comprehensive secondary schools and have a standard Sex and Relationships (SRE) policy and SRE curriculum in place.

Researchers will make contact with SRE co-ordinators at the schools who will describe the study and invite participation. SRE co-ordinators who wish to participate will be required to obtain permission from the school head teacher. They will be asked to identify classes receiving SRE in their school where pupils are aged 13–16 years old. SRE teachers must confirm that the chlamydia lesson has not previously been delivered to these pupils and that they have not received any teaching on STIs. Full details on the requirements of participating schools will be provided. Schools will be offered a £100 Amazon voucher in recognition of the time and resource commitment required. They will also be offered an individual school report based on anonymised and aggregated pupil data from this study which may be helpful in informing their SRE policy and curriculum.

Participating SRE teachers will schedule one lesson (45 minutes) per class to provide study information, obtain consent and collect baseline measures. Pupils will be told that the study aims to evaluate teaching on STIs in their school, but not informed that there are two intervention arms. Pupils will also be told about the number and nature of assessments that will be made, and how their data will be protected and treated. They will be provided with a written participant information sheet and asked to sign a consent form.

Pupils will not be obliged to take part. Quizzes will be administered at the same time as questionnaires at all data collection time points to occupy pupils who do not wish to participate. Pupils will not be required to provide their name (participant responses at each time point will be linked through the demographic information supplied). Pupils will be seated in a manner that prevents classmates from overseeing their responses i.e. in exam conditions. All materials (questionnaires and quizzes) will be placed in a sealed envelope by the individual participants and posted into sealed boxes on completion. Teaching staff will not have access to these. Although parental consent will not be required, as parents of participating pupils will have already consented for their children to participate in SRE and related evaluation activities, a letter outlining the study and their child’s involvement will be sent to all parents through each school as a matter of courtesy. Parents will be given the opportunity to ‘opt-out’ their child at this point.

Baseline measures will be: Demographic information (age, date of birth, gender, and ethnicity), perceived likelihood, perceived severity, response efficacy, self-efficacy, past behaviour, and intention to use condoms during vaginal sex with casual sexual partners for whom STI status is unknown. Provisional measures to be taken at baseline, post-intervention and follow-up are provided in Additional file 1.

After the collection of baseline data, schools will be randomised to receive either the school’s usual teaching on STIs and the chlamydia lesson (intervention arm) or the school’s usual teaching on STIs alone (control arm). This enables the study to evaluate the effectiveness of the chlamydia lesson over and above usual practice. As described above, pupils will be blinded to intervention condition. It is not possible to blind teachers to intervention condition but they will be made aware of the importance of delivering teaching that is consistent with their usual practice. Researchers liaising with schools will offer the same guidance and level of support regardless of intervention condition.

As with all trials of this type, there is the potential for drop-out of whole schools during the study. We have no way of estimating the level of this. Drop-out due to unforeseen circumstances will be planned for and a reserve list of schools will be created to expedite the process of additional recruitment if required.

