### Sample size calculation

The calculation is based on the primary research question. Power analysis using GPower 3.1.2 has indicated that 484 participants will provide 95% power to detect a small to medium effect of 0.3 [21] where α = 0.05. The effect size of 0.3 is based on a recent meta-analysis examining the effectiveness of interventions in changing risk appraisals, intentions and behaviour [22]. Due to the tendency for individuals within a cluster to be more similar to each other than those in other clusters, it is necessary to make adjustments to avoid an overestimation of power [23]. In order to obtain this adjusted sample size, the sample size determined by usual procedures is inflated by multiplication with a factor. This factor is known as the “design effect” and is calculated as:

$$1+\left(n–1\right)\mathrm{ICC}$$

where *n* is the average cluster size, and ICC is the intraclass correlation coefficient. The ICC for intention to use condoms between schools is not known but an estimate of 0.01 is reasonably conservative [23]. With ten schools and an average cluster size of 60 (×2 classes of 30 pupils), the design effect is:

$$1+\left(60–1\right)0.01=1.59$$

Accordingly the adjusted sample size is 484 × 1.59 = 770. We will over-recruit to allow for drop-out between the start of the study and the three month follow-up.

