#### To examine the effect of the intervention

Analysis of Covariance (ANCOVA) will be performed to examine differences in condom use intentions (at time two and at follow-up), and behaviour. This will control for demographic variables (gender, ethnicity, age), behaviour at time one, and measures of risk appraisal, and coping appraisal.

If the lesson is effective in increasing condom use intentions, mediation analysis [28] will be conducted to identify whether changes in risk appraisals and/or coping appraisals are responsible for this change. This will help to identify the mechanism of change and indicate where future research and/or resources should be focussed.

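### The demographic key that links each pupil's three questionnaires is not unique within a school, so a small share of baseline-to-outcome links will be ambiguous or lost; a few private code items would largely cure this

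*Protocol article*

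**What the plan says.** In the protocol article, under Participant recruitment and baseline assessment, the questionnaires are nameless: "Pupils will not be required to provide their name". The link between waves is described in the same sentence: "participant responses at each time point will be linked through the demographic information supplied". The baseline list in that section opens with the items concerned: "Demographic information (age, date of birth, gender, and ethnicity". No study number, self-generated code, or rule for duplicate or inconsistent keys is stated.

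Schools are asked to identify "classes receiving SRE in their school where pupils are aged 13–16 years old", and data collection is scheduled class by class. The Sample size calculation section gives the numbers per school: "With ten schools and an average cluster size of 60 (×2 classes of 30 pupils". A school code exists in the data set until an independent researcher removes it before analysis (Statistical analysis).

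The analysis needs the link. The section on examining the effect of the intervention says of the ANCOVA: "This will control for demographic variables (gender, ethnicity, age), behaviour at time one, and measures of risk appraisal, and coping appraisal". Mediation analysis is to follow if intentions improve. Under Statistical analysis, pupils with missing post-delivery or follow-up data have means imputed.

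**The concern.** Pupils enter in whole classes of similar age, so their birth dates lie close together. Two pupils of the same gender and ethnic group who share a birth date cannot be told apart. Age adds nothing once date of birth is known, and it changes for any pupil who has a birthday between waves. Ethnicity separates few pupils in a homogeneous school. The items are self-reported, so one wrong or blank date of birth breaks the link.

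What is at stake is the joining of a pupil's baseline to the same pupil's later answers. Control for past behaviour is presented in the article as a distinguishing strength of the study, and it depends on this join, as does any analysis of within-pupil change in appraisals. A later questionnaire that cannot be joined leaves its baseline record looking like a pupil with missing data. Under the stated rule, an answer that was in fact collected could then be replaced by an imputed mean.

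**Working it through.** **Inputs from the protocol article.** Ten schools, 60 pupils per school in two classes of 30, ages 13 to 16, design effect 1.59, unadjusted sample size 484, effect size 0.3. The article gives no figure for uniqueness or linkage.

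**Assumptions, shown as a range.** Birthdays uniform; birth dates within a school spread over one to three years; gender 50/50; ethnicity either uninformative, split 80/10/5/5, or split 50/30/20.

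**The plan's own figure first.** The design effect is 1 + 59 × 0.01 = 1.59, and 484 × 1.59 = 769.6, which agrees with "Accordingly the adjusted sample size is 484 × 1.59 = 770".

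**Shared keys within a school.** Write p for the probability of each combination of date of birth, gender and ethnicity. Then:
- expected pairs = C(n,2) × Σp²
- expected pupils sharing a key = n × (1 − Σp(1−p)^(n−1))

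For n = 60, C(60,2) = 1770. With one birth year and no information from ethnicity, Σp² = 1/(365 × 2) = 1/730. Pairs = 1770/730 = 2.42, and pupils sharing = 60 × (1 − (729/730)^59) = 4.66, or 7.8%. With three birth years and a 50/30/20 mix, Σp² = (0.25 + 0.09 + 0.04)/(1095 × 2) = 0.38/2190. Pairs = 0.31, and pupils sharing = 0.61, or 1.0%.

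| Birth-date spread | Ethnicity mix | Pairs per school | Pupils sharing per school | Share |
|---|---|---|---|---|
| 1 year | uninformative | 2.42 | 4.66 | 7.8% |
| 1 year | 80/10/5/5 | 1.59 | 3.08 | 5.1% |
| 1 year | 50/30/20 | 0.92 | 1.81 | 3.0% |
| 3 years | uninformative | 0.81 | 1.60 | 2.7% |
| 3 years | 80/10/5/5 | 0.53 | 1.05 | 1.7% |
| 3 years | 50/30/20 | 0.31 | 0.61 | 1.0% |

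Over ten schools this is about 3 to 24 pairs, or 6 to 47 of 600 pupils. Even in the lowest case the chance of at least one duplicate in the trial is about 1 − exp(−3.1) = 95%. Ten schools of 60 give 600 pupils, not 770; at 77 per school (770/10) the share is 1.3% to 9.9%, or 10 to 76 of 770.

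**Within a class of 30 from one year group.** C(30,2) = 435. Pairs per class run from 435 × 0.38/730 = 0.23 to 435/730 = 0.60. The share of pupils is 1.5% to 3.9%. Over 20 classes that is about 4.5 to 12 pairs, so class matching helps but does not remove the problem.

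**How many shared keys become silent wrong joins.** Between two given waves, a false join with no visible duplicate needs one pupil of the pair present only at the first wave and the other only at the second. If each pupil is absent from a wave independently with probability q, this has probability 2 × [q(1−q)]². The article gives no absence rate. Taking q = 10% as an assumption gives 2 × 0.09² = 0.016; q = 20% gives 2 × 0.16² = 0.051. Applied to the highest count of 24.2 pairs, that is 0.4 and 1.2 pairs.

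**Age as a matching item.** With uniform birthdays, 3/12 = 25% of pupils change age over three months and 2/12 = 17% over two. The article gives both lengths of follow-up.

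**Effect of lost records on power.** The effective number per arm is 770 × (1 − loss)/(1.59 × 2), and power ≈ Φ(0.3 × √(effective number per arm/2) − z). The article does not say whether α is one- or two-sided, so both are shown.

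| Loss | One-sided | Two-sided |
|---|---|---|
| 0% | 95.1% | 91.0% |
| 5% | 94.2% | 89.6% |
| 10% | 93.1% | 87.9% |

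**The case against.** The strongest reply is that a shared key is not a mislink. Where both pupils respond at a wave, the duplicate is visible and can be set aside. The calculation above supports this: silent wrong joins would number about one pair or fewer under the assumed absence rates. Randomisation is by school, so if linking is done within school, no outcome can move into the wrong arm. Power hardly changes, and the plan already over-recruits for drop-out. All of this stands, and it limits the harm.

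It can also be said that a condensed article leaves duplicate handling to the full protocol, and that the questionnaires in Additional file 1, which was not available for this review, may hold another linking item. The first part carries little weight, because the article itself states the key and lists its contents. The second stands as a reservation.

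Three stronger readings are tempting but not supported:
- **That some 7.6% of pupils (59 of 770) will be mislinked.** That figure, 1 − (364/365)^29, counts pupils who share gender and birth date when all 60 come from one year group. It ignores ethnicity and class, applies a 60-per-school rate to 770 pupils, and counts ambiguity rather than error.
- **That the key defeats the purpose of omitting names.** A full birth date with gender and school could identify many pupils to someone holding both a questionnaire and a register. However, the article provides for sealed envelopes and boxes and gives teaching staff no access.
- **That pupils who leave the date blank are those with most to disclose.** This is plausible, but nothing in the document shows it.

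**Conclusion.** The stated linkage key is not unique at the planned school size, and some ambiguous links are close to certain across ten schools. Between 92% and 99% of pupils at 60 per school would still have a unique key. The remaining 1% to 8% (1.5% to 4% within a single-year class), together with an unknown number of misreported or blank dates, will have ambiguous or lost links. The consequence is a somewhat weaker baseline adjustment and mediation analysis, and possibly some collected answers treated as missing and mean-imputed. It does not threaten the allocation of outcomes to arms and costs little power. The range rests on uniform birthdays, the assumed birth-year spreads and ethnicity mixes, and on there being no other identifier in the questionnaires. This is a modest weakness, worth correcting because prevention is nearly free and anonymous records cannot reliably be re-linked afterwards.

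**What to change.** Keep the demographic items, including date of birth, which is a stable identifier. Add two or three self-generated code items that are private, stable and easy to recall, asked in the same words at all three time points. Record school and class on each questionnaire.

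Match within school and class on the combined key, before the school codes are removed. Match exactly first; then, among records still unmatched, allow one item to disagree. Set aside duplicates that remain unresolved, and report how many there are by arm. Do not match on age. Say in the plan how a collected but unlinked outcome is handled, so that it is not overwritten by an imputed mean.

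If the code items together take k about equally common values, the expected number of exact duplicates is divided by about k. Even the highest figure of 24.2 pairs falls below one once k reaches 25 (24.2/25 = 0.97).

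The cost is a few extra short items and some inconsistent code answers, which the one-item tolerance should partly absorb. Pre-numbered questionnaire sets would also give unique links, but handing each pupil the right set at three waves needs a list or labelled envelopes tying names to numbers, which the nameless design avoids.
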